## Methods

### Study design

This protocol is described according to the SPIRIT (Standard Protocol Items: Recommendations for Interventional Trials) Statement (see Additional file 1). The study is an international, multicenter trial conducted between March 2017 and August 2018 in the Netherlands and Sweden. Rehabilitation centers focused on geriatric rehabilitation are asked to participate in this study. In order to ensure the quality and expertise of the participating centers, a minimum inclusion rate of at least 20 patients per year is expected. Therefore, the number of eligible patients is screened in each center before their participation in the study. Measurements will be performed by trained physical therapists at the site and all physical therapists are experienced in geriatric trauma care. Before the start of the study, all physical therapists agreed on the study treatment regime during multiple consensus meetings and were trained to uniformly implement this study treatment. Participating geriatric rehabilitation clinics are listed in Table 1.

**Table 1 Tab1:** Participating rehabilitation clinics

Clinic	Place	Allocation (group)
Zorgspectrum *Geinsche Hof* *[name]* *[name]*	Nieuwegein (NL)	Intervention
Warande *Bovenwegen* *[name]* *[name]*	Zeist (NL)	Intervention
Warande *Diakonessenhuis* *[name]* *[name]*	Zeist (NL)	Intervention
Beweging 3.0 *Meander Medical Center* *[name]* *[name]*	Amersfoort (NL)	Control
Evean *[name]* *[name]*	Amsterdam / Zaandam (NL)	Intervention
Beweging 3.0 *Woonzorgcentrum De Pol* *[name]* *[name]*	Nijkerk (NL)	Control
Cordaan *In het Zomerpark* *[name]* *[name]*	Nieuw-Vennep (NL)	Control
azM Herstelzorg *[name]* *[name]*	Maastricht (NL)	Control
Zorggroep Groningen *[name]* *[name]*	Groningen (NL)	Intervention
Careyn *Nieuw Tamarinde* *[name]* *[name]*	Utrecht (NL)	Control
Telge Rehab *[name]* *[name]*	Södertälje (SE)	Control

Participating geriatric rehabilitation clinics in The Netherlands and Sweden. Clinics were allocated to either the control or the intervention group

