This trial is a two-arm, parallel-design, prospective RCT. Based on a previous pilot study, the average length of rehabilitation is 44 days, with a standard deviation of 17. Using a power of 0.80, an alpha of 5%, and an expected reduction of seven days (one week) in two-sided testing, a sample size of 94 participants per group was calculated. Participants will be allocated to either the control group or the intervention group using a stratified cluster randomization according to the sealed opaque envelope principle. First, all rehabilitation clinics were divided into two groups depending on the inclusion rate: < 2 vs. ≥ 2 eligible participants per month. This division was made to avoid skewing of inclusion rate in both arms. Then in both groups, clinics were randomized by the principal investigator into the control or intervention group using the sealed opaque envelope principle. This resulted in six rehabilitation clinics in the control group and five rehabilitation clinics in the intervention group (Table 1). Randomization per center, or cluster randomization, was chosen for two reasons. First, individual selection bias by the physical therapist is minimized. Second, and more importantly, the physical therapists and participants within one center can now provide a single treatment, either care as usual or care as usual, with real-time visual biofeedback. Considering the constant interaction between physical therapists, as well as between participants, individual randomization would increase the risk of data collection errors.

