### Protocol

Data will be gathered according to a strict study protocol (Fig. 1). Candidate patients who fulfill the inclusion criteria will be asked to participate in the study by the site investigator and receive an information letter with the study protocol and study objectives. If patients agree to participate in the study, informed consent will be signed and the cognitive score will be evaluated by the MMSE. The MMSE is an objective score to quantitatively asses the severity of cognitive impairment. A MMSE score < 18 indicates severe cognitive impairment [16] and this leads to exclusion of the patient in this trial. After informed consent and MMSE, data will be collected from participants according to the following trial protocol. The institutional protocol for physical therapy after proximal femur fractures will be followed in all participants. In addition, each participant receives daily force measurements using the SensiStep system in a 30-m walk to measure the gait parameters. Additional clinical tests will be executed to gain additional insight in the rehabilitation progress of each participant:Functional Ambulation Categories (FAC, once per week)Elderly Mobility Scale (EMS, twice per week)Visual Analogue Scale (VAS, daily)

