### Statistical analysis

Statistical analysis on outcome measures will be conducted using Statistical Package for the Social Sciences (SPSS). First, data distribution will be assessed. Second, missing data will be handled by a multiple imputation technique. The primary analysis will be based on an intention-to-treat principle. Also, a per-protocol analysis will be performed as sensitivity analysis to assess the robustness of the results to protocol deviations [17]. The primary goal is to find a relation between the gait parameters (maximum peak load and step duration) and the discharge date. In addition, other spatiotemporal gait parameters measured by the SensiStep will be analyzed for this relation as well. The secondary goal is to find a relation between the gait parameters and the clinical measurements (i.e. EMS, FAC, and VAS). Relations between all data will be examined using multiple regression analysis.

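### The one analysis named has no term for the randomised clinics or the daily repeated measurements, so an arm comparison run that way gives confidence intervals that are too narrow

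*Protocol article*

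**What the plan says.** Under Methods, Study design, participants are allocated by "stratified cluster randomization according to the sealed opaque envelope principle". Clinics were first split into two strata by expected recruitment (under 2, or at least 2, eligible patients per month) and then randomised. "This resulted in six rehabilitation clinics in the control group and five rehabilitation clinics in the intervention group", and Table 1 agrees with that count. The same section calculates 94 participants per group from an SD of 17 days, a 7-day reduction, 80% power and a two-sided alpha of 5%. It mentions no ICC and no design effect.

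Under Methods, Protocol, "each participant receives daily force measurements using the SensiStep system in a 30-m walk to measure the gait parameters". Pain (VAS) is also recorded daily, the EMS twice a week and the FAC once a week.

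Under Methods, Outcome measures, the discharge date is set by each institution's own team following its normal practice, independently of the trial.

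Under Methods, Statistical analysis, the plan is SPSS, multiple imputation, intention to treat as the primary analysis and per protocol as a sensitivity analysis. "The primary goal is to find a relation between the gait parameters (maximum peak load and step duration) and the discharge date". The section ends with the only inferential method named: "Relations between all data will be examined using multiple regression analysis". No clinic effect, stratum term, mixed model, generalised estimating equation, cluster-robust error, clinic-level summary or repeated-measures structure appears.

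**The concern.** Multiple regression in its usual form treats rows as independent. These data have two levels of dependence: repeated measurements within patients, and patients within clinics. Treatment varies only between clinics, so the arm contrast rests on 11 units and not on 188.

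Clinic correlation is plausible here. Length of stay is the quantity that powers the trial, discharge is decided locally, and each clinic follows its own physical therapy protocol. If clinics differ in discharge practice, an unadjusted patient-level comparison will too often attribute that difference to biofeedback. A nominally significant earlier discharge could then reflect which clinics happened to be drawn into which arm.

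**Working it through.** **1. The plan's own figure.** Inputs from Study design: difference 7 days, SD 17, two-sided alpha 0.05, power 0.80.

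Normal approximation: n = 2 × (1.960 + 0.842)² × 17² / 7² ≈ 92.6, so 93 per group. The two-sample t-test version gives 93.55, so 94. Power at 94 per group is 0.806 by the normal approximation. The stated 94 is therefore the answer for an individually randomised trial with a design effect of 1. The sample size and the named analysis leave out the same thing.

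**2. Arm comparison, one value per patient.** Mean clinic size m = 188 / 11 = 17.1. The ICC is not in the document, so a range is assumed.

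- Design effect: DE = 1 + (m − 1) × ICC
- True type I error of the unadjusted test: 2 × [1 − Φ(1.96 / √DE)]
- Power of a valid clinic-level test for 7 days: non-central t with 9 degrees of freedom (11 clinics minus 2), SE = 17 × √(2 × DE / 94)

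Example at ICC 0.05: DE = 1 + 16.09 × 0.05 = 1.805 and √DE = 1.343. Type I error = 2 × [1 − Φ(1.459)] = 14.5%. SE = 17 × √(2 × 1.805 / 94) = 3.33 days.

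| Assumed ICC | DE | True SE / naive SE | True type I error, unadjusted | Power, clinic-level test |
|---|---|---|---|---|
| 0.01 | 1.16 | 1.08 | 6.9% | 65% |
| 0.02 | 1.32 | 1.15 | 8.8% | 59% |
| 0.05 | 1.81 | 1.34 | 14.5% | 47% |
| 0.10 | 2.61 | 1.62 | 22.5% | 35% |

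**3. Check by simulation.** 20,000 null trials per ICC, with six control clinics of 15-16 patients and five intervention clinics of 18-19:

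| Assumed ICC | Unadjusted patient-level t-test | t-test on clinic means |
|---|---|---|
| 0 | 5.0% | 5.0% |
| 0.01 | 6.6% | 4.7% |
| 0.05 | 14.8% | 5.1% |
| 0.10 | 22.8% | 5.2% |

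A separate run of 8,000 null trials at ICC 0.02 gave 9.1% for the unadjusted test and 5.1% for clinic means. Formula and simulation agree.

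**4. Gait-discharge relation, one value per patient.** Gait varies between patients within a clinic, so the approximate inflation depends on the product of the two ICCs: DE ≈ 1 + (m − 1) × ICC(gait) × ICC(discharge). With both assumed to be 0.10, DE ≈ 1 + 16.09 × 0.01 = 1.16. That corresponds to a type I error of about 7%, against 22.5% for the arm effect at an ICC of 0.10.

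**5. Daily values entered as independent rows.** This handling is not stated in the article. For an arm contrast, ignoring clinic correlation, DE = 1 + (T − 1) × ρ, with T walks per patient and within-patient correlation ρ, both assumed.

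- Low end, T = 14, ρ = 0.3: DE = 1 + 13 × 0.3 = 4.9, type I error 38%.
- High end, T = 44 (the mean stay in the sample-size paragraph), ρ = 0.7: DE = 1 + 43 × 0.7 = 31.1, type I error 73%.

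**The case against.** The best defence is that this is a condensed journal article. It says multiple regression, not ordinary least squares on independent rows, and it does not say that clinic or stratum will be left out. A separate analysis plan could specify a mixed model, and covariate lists or degrees-of-freedom corrections normally belong there. That protects the article on detail, but not on the main point. The article commits to one method for all data in a cluster-randomised trial, and its sample size, which is complete enough to reproduce, also takes patients as independent. That is a planning gap and not only brevity.

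A second defence is that the Statistical analysis section frames the regression as a relation between gait and discharge, not as a comparison of arms. This stands in part: clinic clustering affects that relation much less (step 4). But the hypotheses in the Background and the Outcome measures section expect a difference between arms, the sample size is for a difference between arms, and intention to treat has meaning only for comparing arms. Either the regression covers that comparison, or the article names no method for it.

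Three stronger readings are tempting, and the document does not support them:

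- A reader might infer that the results must be far too optimistic. That depends on an ICC the article does not give; at 0.01 the error rises only to about 7%.
- A reader might infer that the daily measurements push the error to 60% or more. That holds only if daily walks are entered as separate independent rows. With one summary per patient the problem disappears.
- A reader might infer that the single Swedish clinic, in the control arm, is part of this error. Its placement follows from randomising clinics and not from the regression. Any size put on a country effect would be invented, and a random clinic intercept would not in general remove such a shift from the estimate.

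**Conclusion.** The point holds in a conditional form. The named analysis does not account for clinic randomisation or for repeated measurement. An arm comparison run without adjustment would have a true type I error of about 7%, 9%, 14-15% and 23% at ICCs of 0.01, 0.02, 0.05 and 0.10, instead of 5%. These figures assume 94 patients per arm spread evenly over the clinics and one value per patient. The direction is certain for any positive ICC; the size is not, because no ICC is given. The 38-73% range applies only to an arm contrast on pooled daily rows and should not be quoted without that condition.

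**What to change.** In the Statistical analysis section, replace multiple regression for arm comparisons with one of two methods:

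- a linear mixed model with a random clinic intercept, the randomisation stratum as a fixed effect and a small-sample degrees-of-freedom correction (Kenward-Roger or Satterthwaite), or
- a t-test on clinic means.

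For the repeated gait, EMS, FAC and VAS data, specify models with patient nested in clinic, or state which single summary per patient will be analysed. Report the estimated ICC.

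The change needs wording and modest programming, and no new data. The real cost is precision. Intervals become wider, and power for the 7-day difference is about 65%, 47% and 35% at ICCs of 0.01, 0.05 and 0.10, against the stated 80%. Part of that loss comes from having only 9 degrees of freedom: at ICC 0.01 the large-sample figure would be about 75%. The plan should state the lower power openly. An additional analysis without the Swedish clinic is optional and is not needed to correct this point.

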### Monitoring

This trial will be conducted according to the principles of the Declaration of Helsinki (amended version by the 64th WMA General Assembly, Fortaleza, Brazil, October 2013) and in accordance with the Medical Research Involving Human Subjects Act. Gathered data will be encrypted and stored on a secure server and is accessible by the Steering Committee.

This trial will be conducted under strict supervision of an experienced Steering Committee from the University Medical Center Utrecht (UMCU), Maastricht University Medical Center+ (MUMC+), and Uppsala University (UU). Acting as a Steering Committee, the principal investigators from UMCU and MUMC+ will discuss the progress of enrollment at least once every two weeks. The Steering Committee will perform a blinded interim analysis on 30%, 60%, and 90% of the included participants. During these interim analysis, reasons for exclusion will be discussed with the site investigators. Other items will be discussed as well, including but not limited to, applied discharge criteria for each patient, adverse events, quality of the retrieved data, missing data, and necessity to include other participating centers.

A monthly newsletter will be written by the Steering Committee and distributed among the participating centers. In this newsletter, the inclusion rate will be shown per center, which is a common and effective way to increase awareness and readiness to include patients in multicenter trials. The trial progress and general results will be communicated by the Steering Committee upon request.

## Discussion

The worldwide incidence of hip fractures among the elderly will increase due to the ageing population [1]. As hip fractures have a high morbidity and mortality, improvements should be made in the treatment of hip fractures. Biofeedback system have previously shown their potential, as weight-bearing significantly improved in partial and full weight-bearing [9]. This could improve fracture healing through mechanotransduction [6]. As stated before, the hypothesis is that real-time visual biofeedback results in a significant improvement in weight-bearing in the elderly after proximal femur fractures, especially with respect to the gait parameters maximum peak load and step duration, compared to standard training methods. Second, it is hypothesized that improvements in spatiotemporal gait parameters will lead to improvements in clinical scores, such as the EMS, FAC, and VAS. The aim of our trial is to validate these hypotheses and investigate the effect of real-time visual biofeedback on weight-bearing during the rehabilitation after proximal femur fractures in the elderly. This potentially leads to improved rehabilitation (e.g. better functional outcome), faster rehabilitation, and lower medical costs.

Although extensive attention has been paid to the study design, some difficulties still remain. One of the difficulties in this trial is the study population. Often, the elderly who sustain a hip fracture due to low energy trauma have (multiple) co-morbidities that could negatively affect gait. It is difficult to detect the amount of influence of these co-morbidities on gait. The question arises if any improvements or deterioration in gait is caused by real-time visual biofeedback or by the co-morbidities. To overcome this issue, the strict inclusion criteria for participants should minimize variability in the data. Moreover, the large number of participants (e.g. 94 per arm) should minimize the effect of co-morbidities on gait.

The topic of adherence could be another issue in this trial, as the trial will cause additional burden to both the participants and physical therapists. It is therefore important to select enthusiastic and experienced rehabilitation centers as candidate centers. This will be determined by asking candidate centers to register all eligible patients before the start of this trial over two months. Furthermore, the Steering Committee will weekly evaluate the inclusion rate and search for missing data, which provides the opportunity to steer directly if any issues are detected.

The potential effect of real-time visual biofeedback on weight-bearing can have a major influence on rehabilitation after proximal femur fractures in the elderly; therefore, dissemination is important. A stakeholder analysis will be performed early in the project and will determine how dissemination to these stakeholders should be handled in order to convince them of the added value of real-time visual biofeedback. The stakeholder analysis will identify which organizations and people the dissemination should target. Dissemination will take place at different levels, most importantly the patient level, the care provider level, and the level of the healthcare organizations, including insurance companies.

In summary, this is a multicenter RCT to investigate the rehabilitation progress and the value of real-time visual biofeedback on weight-bearing during rehabilitation after proximal femur fractures in the elderly. Primary focus lies on the gait parameters maximum peak load and step duration in relation to discharge date; however, secondary outcomes in other spatiotemporal gait parameters and additional validated clinical tests will be analyzed as well. This trial will contribute to existing knowledge of rehabilitation after hip fractures in the elderly, hopefully contributing to improved outcome for many affected.

## Trial status

This protocol (V1, 18/10/2016) started in March 2017 and the recruitment will approximately be completed in August 2018.

## Abbreviations

EMS: Elderly Mobility Scale
FAC: Functional Ambulation Categories
MMSE: Mini Mental State Examination
MUMC+: Maastricht University Medical Center+
RCT: Randomized controlled trial
UMCU: University Medical Center Utrecht
VAS: Visual Analogue Scale
